## Abstract

**Introduction::**

Resistance to targeted and immune checkpoint blockade treatment remains a major problem in patients with advanced metastatic melanoma. To overcome this problem, there needs to be a decrease in burden of disease as well as re-establishing of immune sensitivity. The aim of this early phase 2 clinical trial is to investigate a novel way of sequencing and combining decitabine and carboplatin to decrease methylation and increase DNA repair resulting in a decrease in the disease burden and to re-establish sensitivity to the immune response.

**Methods and analysis::**

This single-site early phase 2 clinical trial will be conducted in 30 patients with metastatic melanoma that are resistant to all approved therapies. Patients will receive 2 × 4-week cycles of decitabine 7 mg/m^2^ IVI/day for 5 days (D1-D5) followed by Carboplatin AUC 5 IVI on D8; Week 3 and Week 4 no treatment. The primary objective is to determine DNA methylation and DNA repair levels before, and immediately after treatment; quantify immune-response markers (PDL-1, PD-1, CD4/CD8, and CD68) in blood, tumor and microenvironment before treatment and after 2 cycles. The secondary outcome objective is to quantify response rate (RR) to administration of 2 cycles of decitabine and carboplatin cycle using response evaluation criteria in solid tumors (RECIST 1.1) criteria. This data will be used to calculate sample size and determine statistical analysis plan for larger Phase 2 study.

**Ethics and dissemination::**

Protocol version 1.1 was reviewed and approved by the Hunter New England Health Human Research Ethics Committee (Reference No: 15/12/16/3.08, NSW HREC Reference No: HREC/15/HNE/505) and site-specific approval from the Calvary Mater Hospital Newcastle, NSW, Australia (NSW SSA Reference No: SSA/16/HNE/224). Primary and secondary outcomes and safety data will be disseminated through publications.

**Trial registration details::**

Australian New Zealand Clinical Trial Registry ACTRN12616000440426

Article summaryThis is a new combination of drugs for the treatment of metastatic melanoma to determine if the tumor becomes immunogenic in order for it to be used as a priming regime in combination with immunotherapy in future.Early phase II, open label single cohort study of 30 patients at single site (Calvary Mater Hospital Newcastle, Australia)This early phase II study will assess the feasibility of a larger Phase II study and determine outcome measures required to calculate sample sizes and develop a statistical plan.

## Introduction

1

Resistance to targeted and immune checkpoint blockade treatment remains a major problem in patients with advanced metastatic melanoma. Melanoma patients with advanced disease, especially after targeted therapy, do not respond as well to immune therapy because of high disease burden and the development of immune therapy resistance.^[1]^ To overcome this problem, there needs to be a decrease in burden of disease as well as re-establishing of immune sensitivity. The aim of this early phase 2 clinical trial is to investigate a novel way of sequencing and combining agents to decrease the disease burden and to re-establish sensitivity to the immune response.

Platinum chemotherapy is used to treat most solid tumors, with germ-cell tumors obtaining cure rates of over 90% when treated with cisplatin. Despite this, it has limited efficacy in melanoma (∼10%) and as a consequence is rarely used in treatment. The mechanism of action for cisplatin and its analogue carboplatin, is insertion of platinum into DNA to form cross-links which is structurally very similar to UV-induced DNA damage. Recognition of DNA cross-links by the global genome repair proteins XPC, DNA-damage binding protein 1 and DNA-damage binding protein 2 triggers apoptosis rather than attempting to repair the damage. Therefore, reduced levels of global genome repair result in a lack of apoptotic signaling, leading to limited or no response to platinum treatment and an increase in “UV-like” mutation load across the platinum-treated genome.

5-aza-2’-deoxycytidine (decitabine) reactivates the expression of genes silenced by hypermethylation. Decitabine is a cytidine analogue that incorporates into replicating DNA and blocks the action of DNA methyltransferases. Previous studies have shown that decitabine enhances the anti-tumor immune response and at low dosage correlates with clinical response in hematological malignancies.

We previously reported very low levels of XPC, DNA-damage binding protein 1, and DNA-damage binding protein 2 in melanoma cell lines that are not inducible by carboplatin or its analogue, cisplatin.^[2,3]^ Subsequent analysis of advanced primary and metastatic melanomas from the Hunter region, NSW, Australia and the Cancer Genome Atlas (TCGA) data from 378 melanomas identified very low levels of XPC expression.^[4]^ Analysis of XPC methylation using Illumina 450K methylation array data from the 378 TCGA melanomas. A region -3000 bp upstream of XPC was fully methylated (β > 0.6) in 125 melanomas (33.1%) and partially methylated (β 0.2–0.6) in 253 melanomas (66.9%). Methylation of the CpG dinucleotides within the proximal XPC promoter region (−1 to −175 bp upstream) was not detected in the TCGA cohort. Further to this, we have found melanoma cell lines contain methylation in the CpG island shores that can be removed via blocking of methyltransferases with decitabine.^[5]^

In pre-clinical studies melanoma cell lines were treated with 0.26 uM decitabine for 72 hours to reduce methylation across the genome, followed by 8 ug/mL carboplatin for 48 hours to induce DNA damage, apoptosis and cellular stress. The doses used were the lowest clinically relevant doses to induce a response. The majority of melanoma cell lines showed an induction of XPC (range = 1.1–3.2 fold increase) and increased apoptotic cell death after the decitabine/carboplatin sequential treatment compared to carboplatin alone (range = 1.6–2.2 fold increase). Only one melanoma cell line showed no increase in XPC or apoptosis after the sequential combination treatment, but did express markers of senescence. All cells lines displayed a significant decrease in cell proliferation after the sequential combination.^[5]^

There is established evidence for safety of decitabine/carboplatin sequential treatment. A phase I dose escalation study in platinum-resistant ovarian cancer reported no dose-limiting toxicity at 10 mg/m^2^ decitibine for 5 days followed by AUC5 carboplatin on Day 8 of a 28 day cycle.^[6]^ This dose regime was repeated in a larger cohort (n = 17) and the most common toxicities were nausea (n = 10), constipation (n = 7), allergic reactions (n = 6), neutropenia, fatigue, anemia (5 patients each), the majority being grades 1–2. Grade 3–4 toxicities affecting more than one patient included neutropenia (n = 4) and thrombocytopenia (n = 2).^[7]^ Therefore, to minimize toxicity further, this protocol uses a lower dose regime of decitabine 7 mg/m^2^ for 5 days followed by Carboplatin AUC5 on day 8. AUC5 of carboplatin is the only dosage previously tested in sequential combination with decitabine^[6,7]^ and to ensure minimal toxicity it is AUC1 lower than the most recent clinical trial outcomes that included carboplatin treatment of melanoma.^[8]^

The primary hypothesis for this protocol is that sequential treatment with decitabine and carboplatin will result in:

i)decrease in methylation and increase in XPC in tumorsii)increase in immune response markers in tumor and blood.

The secondary hypothesis is that sequential treatment with decitabine and carboplatin will induce an overall response of reduction of tumor size or number (assessed by RECIST) or stable disease indicated by no increase in tumor size or number (assessed by RECIST).

## Methods and analysis

2

### Study objectives

2.1

#### Primary outcome objectives

2.1.1

1.Determine DNA methylation and XPC levels before, and immediately after treatment, that is, at study entry and after 2 months.2.Quantify immune-response markers (PDL-1, PD-1, CD4/CD8, and CD68) in blood, tumor and microenvironment and immune response in blood before treatment and after 2 cycles.

#### Secondary outcome objectives

2.1.2

1.Quantify response rate (RR) to administration of 2 cycles of decitabine and carboplatin/28 day cycle using RECIST criteria. This data will be used to calculate sample size and determine statistical analysis plan for larger Phase II study.

This is a single-center study conducted at Calvary Mater Hospital, Newcastle NSW Australia in a single group of 30 patients. Surgical biopsies will be conducted as day surgery and all participants will receive treatment as day oncology patients. There will be no requirement for participants to be admitted to hospital.

### Treatment protocol

2.2

Patients will receive a four week treatment protocol consisting of Decitabine 7 mg/m^2^ IVI/day for 5 days (D1-D5) followed by Carboplatin AUC 5 IVI on Day 8 (D8). Week 3 and Week 4 there is no treatment (Table 1). This four week protocol is repeated once starting at Week 5, Day 29 (Table 1).

**Table 1 T1:**

Study outline.

Adverse events will be assessed on Day 1, Day 8, Day 29, Day 36, and Day 57 (Table 1) and graded according to common terminology Criteria for AEs, National Cancer Institute (NCI-CTCAE) v4.

### Data collection

2.3

Before treatment (Day -14) and on Day 57 (week 9) an excision biopsy of subcutaneous metastatic lesion or lymph node and 9 mL blood collection will be collected where. Tumor biopsies will be used for analysis of DNA methylation (whole genome bisulfite sequencing and ELISA assay), XPC mRNA and protein levels. Statistically significant differences in methylation and XPC levels will be tested before and after treatment using paired *t* test with Bonferroni correction.

Tumor biopsies will also be used for immunohistochemistry to assess the immune-response markers: CD4 and CD8 inside tumor, number of tumor cells with PDL1 expression, CD8 with PDL1 expression, CD8 with CD45RO expression, CD8 with granzyme B, TIM3, perforin as described in Tumeh et al.^[9]^ Blood collected will be tested for immune activation profile and INF gamma signature. All data will be tested before and after treatment using paired t-test with Bonferroni correction.

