### Sample size calculation

2.6

This is a signal-seeking Early Phase 2 study to inform sample size calculation for a larger Phase 2 study after completion. Power calculation based on incidence of response: Assuming ORR is <1% in untreated immunotherapy-resistant melanoma, using Simon 2-stage design, initial recruitment (n = 17) is 80% powered to detect ORR of 20% (α = 0.05). The second stage will be initiated if there is at least one response in the first 17 patients. In the second stage, 23 additional patients (n = 40) will be enrolled to achieve 80% power to detect 10% ORR (α = 0.05).

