### Data analysis plan

2.7

All data for primary outcomes will be tested before and after treatment using paired t-test with Bonferroni correction when required.

Objective response rate (ORR) is defined as the proportion of patients with tumor size reduction of 30% after onset of treatment until documented tumor progression. ORR will be calculated using RECIST scores at weeks −1 and 9. Before-after study (paired *t* test): RECIST scores will undergo paired t-test analysis to determine statistical differences in response based on tumor size. The results of the before-after study will be used to calculate the sample size for a large multi-center Phase 2 trial.

Waterfall plot of tumor shrinkage is a data visualization technique that depicts tumor shrinkage that is the best observed % change of sum of target lesions from baseline.

Overall survival will be calculated at each RECIST data collection point (weeks −1 and 9) and every 6 months until study completion. Overall survival will be calculated as the time from initiation of the trial treatment to death from any cause. Kaplan-Meier plots for sub-groups based on primary outcome data will be generated every 6 months for the duration of the study.

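### Holm's step-down could replace single-step Bonferroni for the primary marker tests: same error control, never fewer rejections, a modest gain in power

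*Protocol article*

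**What the plan says.** Section 2.3 (Data collection) names the procedure twice. For the first group of markers it says "Statistically significant differences in methylation and XPC levels will be tested before and after treatment using paired" t tests, and the sentence goes on to name Bonferroni. After the immune markers it says "All data will be tested before and after treatment using paired t-test with Bonferroni correction". Section 2.7 (Data analysis plan) says "All data for primary outcomes will be tested before and after treatment using paired t-test with Bonferroni correction when required", which makes the correction conditional without giving the condition.

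The measures come from three sentences of section 2.3:
- "Tumor biopsies will be used for analysis of DNA methylation (whole genome bisulfite sequencing and ELISA assay), XPC mRNA and protein levels"
- for tumor immune markers, "CD4 and CD8 inside tumor, number of tumor cells with PDL1 expression, CD8 with PDL1 expression, CD8 with CD45RO expression, CD8 with granzyme B", followed by TIM3 and perforin
- "Blood collected will be tested for immune activation profile and INF gamma signature"

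The article does not say how many tests form a family, whether there is one family or several, or which alpha applies to the markers. The only alpha is in section 2.6 and belongs to the response rate: "80% powered to detect ORR of 20% (α = 0.05". Section 2.6 gives no power or effect size for any marker. Holm's procedure is not mentioned, and no simultaneous confidence intervals are planned.

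**The concern.** The question is which correction is named, not whether one is applied. Single-step Bonferroni holds every p-value to the strictest threshold, even after other hypotheses in the family have been rejected. Holm relaxes the threshold after each rejection, needs no added assumption and keeps the same familywise error.

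The hypotheses in the Introduction expect several markers to change: methylation, XPC and immune markers. Holm helps in that situation, because its gain comes with the second and later rejections. With few pairs, some real marker changes could be reported as non-significant under Bonferroni that Holm would have declared significant at the same error rate.

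**Working it through.** **1. No stated figure to reproduce.** The article gives no power for the markers, so everything below is illustrative.

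**2. Why Holm never rejects less.** Order the m p-values from smallest to largest.
- Bonferroni compares each with 0.05/m.
- Holm compares the i-th smallest with 0.05/(m − i + 1) and stops at the first failure.
- Each Holm threshold is at least 0.05/m, so any p-value that passes Bonferroni also passes Holm.
- For m = 4, Holm's thresholds are 0.0125, 0.0167, 0.025 and 0.05. Bonferroni uses 0.0125 throughout.

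**3. Why the error rate is the same.** Suppose m0 of the m null hypotheses are true. Holm's first false rejection comes no later than step m − m0 + 1, where the threshold is at most 0.05/m0. The chance that any of m0 true nulls falls below 0.05/m0 is at most m0 × 0.05/m0 = 0.05, whatever the dependence.

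**4. Why the first rejection is unaffected.** Both procedures compare the smallest p-value with 0.05/m, so the chance of at least one significant marker is identical.

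**5. Inputs for the size of the gain.**
- Pairs: 30, from section 2.1.2 ("in a single group of 30 patients"). Section 2.6 gives 17 and 40, which are also run.
- Family size: not given. Counting section 2.3 gives 2 methylation assays + 2 XPC measures + 8 tumor immune measures + 2 blood measures = 14. The methylation and XPC measures alone give 4. The count is uncertain: section 2.1.1 also lists PD-1 and CD68, and the article does not say how the sequencing data are summarised.
- Assumed: two-sided familywise alpha 0.05, normal paired differences, a standardised change of 0.6 (0.8 for 17 pairs), and equal correlation of 0.3 to 0.6 between markers.

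**6. Exact Bonferroni power per marker** (noncentral t, 29 degrees of freedom, noncentrality 0.6 × √30 = 3.286):
- m = 14: critical value 3.171, power 55.3%
- m = 4: critical value 2.663, power 72.9%

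**7. Bonferroni against Holm by simulation** (20,000 runs per setting, 30 pairs, 0.6 SD, correlation 0.3 to 0.6). Average power per truly changed marker:

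| Family | Markers that move | Bonferroni | Holm | Gain (points) |
|---|---|---|---|---|
| 14 | 4 | 55% | 57% | 2 |
| 14 | 7 | 55% | 59% | 4 |
| 14 | 10 | 55% | 62–63% | 7 |
| 14 | 14 | 55% | 69–70% | 13–15 |
| 4 | 1 | 73% | 73% | 0 |
| 4 | 2 | 73% | 75–76% | 2–3 |
| 4 | 4 | 73% | 82–84% | 9–10 |

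Holm missed no Bonferroni rejection in any run. Its simulated familywise error was at most 4.5% in these settings. The chance of at least one significant marker was the same for both, for example 90.7% with 4 of 14 moving at correlation 0.3.

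**8. Other numbers of pairs, family of 14, with 4, 7 and all 14 moving.** At 17 pairs and 0.8 SD the gains are 2, 4 and 14 to 15 points. At 40 pairs and 0.6 SD they are 2, 4 and 12 to 14 points.

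**9. Effect of correlation.** With 30 pairs, 0.6 SD and all 14 moving, Holm's gain is 15.6, 14.9, 13.5 and 11.7 points at correlations 0, 0.3, 0.6 and 0.8. It shrinks as correlation rises.

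**The case against.** The strongest reply is that nothing here is wrong. Bonferroni is a valid, conservative and standard prespecification. No stated power or sample size rests on it. The study is described as signal-seeking, and its second stage depends on tumor responses, not on marker p-values. All of this stands, and it limits the point to an efficiency improvement.

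A reader might infer more in four ways, none of which the article supports.

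- **That one family covers all primary markers.** Section 2.3 names the correction separately for two groups of markers, and section 2.7 makes it conditional. Neither states a single family. Imposing one could lower power. Bonferroni over 4 methylation and XPC tests gives 72.9% (30 pairs, 0.6 SD), whereas Holm over 14 gives 59% with 7 moving and 69 to 70% with all moving. At 17 pairs and 0.8 SD the comparison is 68.3% against 62 to 63% at best. Splitting controls the error per family rather than overall, which is for the sponsor to choose.
- **That the trial may fail to find any signal because of Bonferroni.** It cannot, since the first rejection is identical under both procedures.
- **That related markers strengthen the case for Holm.** Holm does not use correlation, and its gain falls as correlation rises.
- **That the gain is about 15 points.** That needs all 14 markers to move by the same amount. With half or fewer moving it is about 4 points or less.

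Bonferroni also has simple matching simultaneous intervals, which Holm lacks. That is a real but small cost, because the protocol plans no such intervals.

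**Conclusion.** The point holds as a minor, near-free efficiency gain. Sections 2.3 and 2.7 name a valid procedure for which a uniformly at least as powerful alternative exists, with the same error control and the same p-values. That comparison is mathematical and holds for any family of two or more tests. The size of the gain depends on assumptions that the article does not supply (family size, effect size, number of markers that move). It runs from nothing, when one marker in a family of 4 moves, to 13 to 15 points when all of 14 move. It is largest when many markers change, which is the direction of the hypotheses. No stated figure is in error and no stated decision rule is affected.

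**What to change.** In sections 2.3 and 2.7, name the Holm step-down correction in place of Bonferroni. Apply it within whatever family or families of tests the sponsor intends and at the same alpha. Do not merge families that the protocol does not merge.

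The cost is a change of wording in two sections and one line of analysis code, made before any marker data are analysed. It needs no patients, data or assumptions beyond those already planned. The only downside is that simple Bonferroni simultaneous intervals, if later wanted, would not match the test decisions exactly.

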#### Secondary outcome protocol

2.3.1

Overall response rate (ORR) will be determined using RECIST 1.1 criteria at completion of the 2 treatment cycles in week 9. This data will be used to calculate sample size for larger Phase II study.

### Inclusion criteria, screening procedures and pre-treatment investigations

2.4

If laboratory investigations have not been performed within the 7 day period prior to starting treatment then they must be repeated prior to day 1 of cycle 1 to ensure the patient is fit to receive platinum based chemotherapy and Decitabine, this does not apply for endocrinology investigations (thyroid function test, adrenocorticotropic hormone, cortisol, s-testosterone) where these investigations can be performed within 21 days prior to starting treatment

Patients need to meet inclusion criteria outline in Table 2. Patients should have CT scans and positron emission tomography scans before treatment starts and the same investigations should be performed using the same provider after 2 cycles of treatment. Target and non-target lesions will be identified clinically and on CT scan (Table 2).

**Table 2 T2:**
[figure not shown]
Inclusion criteria, screening procedures, and pre-treatment investigations.

Target AUC X (GFR + 25) for Carboplatin dose, for the purpose of this protocol the GFR is considered equivalent to the creatinine clearance. The GFR should be calculated as per local practice and the exact dose of Carboplatin depends on the GFR and the dose should be checked with the Medical Oncology Clinical Trial Pharmacist. If the estimated creatinine clearance is < 50 ml/minute, then a formal measurement of the GFR is required using an isotopic clearance and if the isotopic clearance is used then the value uncorrected for body surface area (BSA) should be used in dose calculations. If the GFR is measured by isotopic clearance, the target AUC is one unit lower than that based on the estimated GFR (4 and not 5).

The GFR should be recalculated for renal toxicity (serum creatinine > 1.5 upper limit of normal), serum creatinine changes of > 10% compared to baseline or last creatinine value used to calculate carboplatin dose (whichever is more recent), for each dose modification of carboplatin and cycle 2 if according to clinical judgment there has been significant doubt about the true GFR at cycle 1.

Dose capping of carboplatin should be done according to standard local practice and should be checked with the Medical Oncology Clinical Trial Pharmacist. The clinical judgment of an experienced clinician should be applied to calculate the Carboplatin dose as patients who have prolonged post-operative recovery and who have been maintained on prolonged IVI fluids with poor nutrition will have falsely low serum creatinine and formulae such as the Cockcroft-Gault formula for GFR are inaccurate at the extremes of age and weight.

### Toxicity

2.5

*Hematological toxicity:* chemotherapy should be delayed if either of the following occurs in the pre-treatment blood count: absolute neutrophil count less than 1.5 × 10^9^/l; platelet count less than 100 × 10^9^/l. Full blood count should be repeated weekly until hematological recovery has occurred. If hematological recovery takes longer than 7 days the dose of Carboplatin should be reduced according to standard criteria by 1 AUC before cycle 2 is given.

Febrile neutropenia is defined as fever with or without clinically or microbiologically documented infection with ANC less than 1 × 10^9^/l and fever >  = 38.5 °C and this should lead to a dose modification of 1 AUC before cycle 2.

*Renal Toxicity*: As described above, the dose of Carboplatin should be recalculated for renal toxicity. There are no specific dose modifications for renal toxicity before cycle 2 and this combination of treatment is not directly expected to cause renal toxicity.

*Hypersensitivity:* A hypersensitivity reaction to Carboplatin should be managed according to standard local practice. Patients may be retreated according to local practice, including escalations of hypersensitivity prophylaxis, in-patient monitoring and increased in the duration of the infusion.

*Hepatotoxicity:* Hepatotoxicity is not expected with this combination.

*Other toxicities*: Nausea, constipation, fatigue, anorexia, diarrhea, vomiting and dizziness were reported as treatment related adverse events in a previous trial where this combination was used. These will be managed by standard local practice guidelines and will be graded according to severity. The majority of these toxicities were grade 1–2. The only grade 3–4 toxicities reported on this combination of treatment before that affected more than 1 patient included neutropenia and thrombocytopenia (management already discussed).

